## VERSION HISTORY/AMENDMENT HISTORY

| Version No. | Version Date  | Explanation of the rationale for amendment and summary of changes                                                                                                                                                                                                                                                                                                                                                                                                                                                                                                                                                                                                                                                                                                                                                                                                                                                                                                                                                                                                                                                  |
|-------------|---------------|--------------------------------------------------------------------------------------------------------------------------------------------------------------------------------------------------------------------------------------------------------------------------------------------------------------------------------------------------------------------------------------------------------------------------------------------------------------------------------------------------------------------------------------------------------------------------------------------------------------------------------------------------------------------------------------------------------------------------------------------------------------------------------------------------------------------------------------------------------------------------------------------------------------------------------------------------------------------------------------------------------------------------------------------------------------------------------------------------------------------|
| 1.0         | May 15, 2024  | Not applicable                                                                                                                                                                                                                                                                                                                                                                                                                                                                                                                                                                                                                                                                                                                                                                                                                                                                                                                                                                                                                                                                                                     |
| 2.0         | June 10, 2024 | 
1: In the informed consent form, the responsibility for adverse events is supplemented as follows: Although this study is conducted with the premise of ensuring the safety of participants, there is still a possibility of unforeseeable serious adverse reactions that may lead to health damage. If a participant experiences an unforeseeable serious adverse reaction related to the study protocol that results in health damage, the responsible physician will conduct active diagnosis and treatment. In the event that a participant suffers harm that is determined by an authoritative institution as stipulated by national laws and regulations to be related to the investigational drug of this study and for which responsibility is to be assumed, the participant will receive free treatment and compensation in accordance with the laws and regulations of China. The investigator (physician) will do their utmost to prevent and treat any harm that may arise from this study.
 
2: The protocol has been supplemented to clarify the risks that the experimental group will
 |

|  |  |                                                                                                                                                                                                                                                                                                                                                                                                                                                                                                                                                                                                                                                                                                                                                                                                                                                                                                                                                                                                                                                                                                                                                                                                                                                                                                                  |
|--|--|------------------------------------------------------------------------------------------------------------------------------------------------------------------------------------------------------------------------------------------------------------------------------------------------------------------------------------------------------------------------------------------------------------------------------------------------------------------------------------------------------------------------------------------------------------------------------------------------------------------------------------------------------------------------------------------------------------------------------------------------------------------------------------------------------------------------------------------------------------------------------------------------------------------------------------------------------------------------------------------------------------------------------------------------------------------------------------------------------------------------------------------------------------------------------------------------------------------------------------------------------------------------------------------------------------------|
|  |  | 
undertake, and both the protocol and the informed consent form have been revised accordingly. The content is as follows: This study aims to explore the possibility of reducing the use of glucocorticoids on the basis of standard treatment, with the expectation of effectively preventing chemotherapy-induced nausea and vomiting (CINV) while reducing the types, incidence, and severity of potential adverse reactions. Although this approach may decrease the incidence and severity of side effects associated with dexamethasone (DEX), the reduction in DEX dosage may increase the risk of poor CINV control in the experimental group. This could potentially lead to decreased adherence to chemotherapy and a reduced quality of life.
 
3: The protocol has been supplemented to include screening for cardiotoxicity. Specifically, electrocardiogram (ECG) tests will be conducted at three distinct time points: during the screening period, before antiemetic treatment on the day of chemotherapy, and 5 hours after chemotherapy.
 
4: The informed consent form has been supplemented to clarify the potential benefits for participants. The potential benefits for subjects in this study are primarily reflected in the reduction of nausea and vomiting caused by
 |
|--|--|------------------------------------------------------------------------------------------------------------------------------------------------------------------------------------------------------------------------------------------------------------------------------------------------------------------------------------------------------------------------------------------------------------------------------------------------------------------------------------------------------------------------------------------------------------------------------------------------------------------------------------------------------------------------------------------------------------------------------------------------------------------------------------------------------------------------------------------------------------------------------------------------------------------------------------------------------------------------------------------------------------------------------------------------------------------------------------------------------------------------------------------------------------------------------------------------------------------------------------------------------------------------------------------------------------------|

|  |  |                                                                                                                                                                                                                                                                                                                                                                                                                                                                                                                                                                                                                               |
|--|--|-------------------------------------------------------------------------------------------------------------------------------------------------------------------------------------------------------------------------------------------------------------------------------------------------------------------------------------------------------------------------------------------------------------------------------------------------------------------------------------------------------------------------------------------------------------------------------------------------------------------------------|
|  |  | 
chemotherapy through a more convenient and sustained method. This, in turn, is expected to further enhance the quality of life, avoid reducing chemotherapy doses, delaying chemotherapy, or even suspending chemotherapy. Indirect benefits include the mitigation of adverse reactions associated with antiemetic medications, such as insomnia, gastrointestinal symptoms, anxiety and irritability, rashes, and increased risk of infection. Additionally, completing chemotherapy at full doses, for the full course, and on schedule will also improve the treatment outcomes and prognosis for cancer patients.
 |
|--|--|-------------------------------------------------------------------------------------------------------------------------------------------------------------------------------------------------------------------------------------------------------------------------------------------------------------------------------------------------------------------------------------------------------------------------------------------------------------------------------------------------------------------------------------------------------------------------------------------------------------------------------|

## Abbreviations

|           |                                                        |
|-----------|--------------------------------------------------------|
| • DEX     | Dexamethasone                                          |
| • NEPA    | Netupitant/Palonosetron Capsules                       |
| • CINV    | Chemotherapy-Induced Nausea and Vomiting               |
| • CRR     | Complete Response Rate                                 |
| • NSNR    | No Significant Nausea Rate                             |
| • CPR     | Complete Protection Rate                               |
| • mITT    | Modified Intention-To-Treat                            |
| • PPS     | Per Protocol Set                                       |
| • ASCO    | American Society of Clinical Oncology                  |
| • NCCN    | National Comprehensive Cancer Network                  |
| • MASCC   | Multinational Association of Supportive Care in Cancer |
| • ESMO    | European Society for Medical Oncology                  |
| • MEC     | Moderately Emetogenic Chemotherapy                     |
| • HEC     | Highly Emetogenic Chemotherapy                         |
| • NK1RA   | Neurokinin-1 Receptor Antagonist                       |
| • 5-HT3RA | 5-Hydroxytryptamine-3 Receptor Antagonist              |

## Protocol Synopsis

|                               |                                                                                                                                                                                                                                                                                    |
|-------------------------------|------------------------------------------------------------------------------------------------------------------------------------------------------------------------------------------------------------------------------------------------------------------------------------|
| Study Title            | Single Low-Dose Dexamethasone (5mg Versus 8mg)
With NEPA For Prevention Of Highly Or Moderately
Emetogenic Chemotherapy (LD-NEPA): A Phase III
Randomised Clinical Trial                                                                                                  |
| Protocol Number        | 2024-102                                                                                                                                                                                                                                                                           |
| Version Number         | V2.0                                                                                                                                                                                                                                                                               |
| Sponsor                | Xiamen University Affiliated Zhongshan Hospital                                                                                                                                                                                                                                    |
| Principal Investigator | [name]                                                                                                                                                                                                                                                                        |
| Nature of the Study    | Investigator-Initiated Study                                                                                                                                                                                                                                                       |
| Study Design           | Prospective, Randomized, Non-inferiority Trial                                                                                                                                                                                                                                     |
| Study Population       | Patients with chemotherapy-induced nausea and vomiting (CINV) due to malignant tumors                                                                                                                                                                                              |
| Research Question      | To explore the clinical efficacy of different low-dose dexamethasone combined with single or double standard doses of netupitant/palonosetron capsules (NEPA) for the prevention of CINV.                                                                                          |
| Study Objectives       | Primary Objective:
To explore the efficacy of different low-dose dexamethasone combined with single dose of NEPA in preventing CINV.
Secondary Objectives:
To evaluate the safety of different low-dose dexamethasone combined with single dose of NEPA in treating CINV. |

## Study Endpoints

### Primary Endpoint:

Complete Response Rate (CRR, defined as no vomiting episodes and no rescue medication use within 7 days after receiving the study drug).

### Secondary efficacy Endpoints:

- CRR during acute (0-24h), delayed (24-120h), and long-delayed (120-168h) phases

### Secondary Safety Endpoints:

- Treatment related adverse events (TRAEs, evaluated using the National Cancer Institute Common Terminology Criteria for Adverse Events (NCI CTCAE) version 5.0).
- Cardiac toxicity monitoring via pre-dose and 5-hour post-dose electrocardiograms (ECGs)
- Blood glucose tracking (hyperglycemia defined as fasting/postprandial glucose exceeding normal ranges) during the first treatment week.

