## Study Flowchart

[figure not shown]

| Project                                                            | Screening Period | Baseline | Treatment Period |    |    |    |
|--------------------------------------------------------------------|------------------|----------|------------------|----|----|----|
| Visit Day                                                          | D-3~D0           | D0       | D1               | D3 | D5 | D7 |
| Informed Consent Signed                                            | x                |          |                  |    |    |    |
| Inclusion/Exclusion Criteria                                       | x                |          |                  |    |    |    |
| Randomization                                                      | x                |          |                  |    |    |    |
| Demographic Data                                                   | x                |          |                  |    |    |    |
| Medical History                                                    | x                |          |                  |    |    |    |
| ECOG Performance Status                                            | x                |          |                  |    |    |    |
| Physical Examination                                               | x                | x        | x                | x  | x  | x  |
| Vital Signs a                                           | x                | x        | x                | x  | x  | x  |
| Blood Glucose                                                      |                  | x        | x                | x  | x  | x  |
| Complete Blood Count b                                  | x                |          |                  |    | x  |    |
| Urinalysis c                                            | x                |          |                  |    |    |    |
| Biochemical Profile d                                   | x                | x        |                  |    | x  |    |
| Coagulation Function e                                  | x                |          |                  |    |    |    |
| Pregnancy Test f                                        | x                |          |                  |    |    |    |
| Thyroid Function Tests g                                | x                |          |                  |    |    |    |

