### **2.2.3 Secondary Safety Endpoints**

Treatment related adverse events (evaluated using the National Cancer Institute Common Terminology Criteria for Adverse Events (NCI CTCAE) version 5.0).

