### 10.5 General Principles for Efficacy Analysis

In this study, unless otherwise specified, efficacy data will be descriptively summarized according to the following general principles:

- Demographic and clinical characteristics were analyzed using descriptive statistics, with categorical variables expressed as frequencies (percentages) and continuous variables as median (interquartile range).

- The efficacy endpoints (CRR, TCR, and CCR) were analyzed for noninferiority using a stratified Mantel-Haenszel approach to compare dose cohorts, adjusting for age. The combined risk difference and its two-sided 95% confidence interval were calculated. Noninferiority was concluded if the lower confidence limit exceeded the pre-specified margin of -15%. Changes in response within subjects across different treatment phases were assessed using McNemar's test. P values for noninferiority tests were reported as one sided, whereas other P values were two sided.
- Group comparisons employed chi-square/Fisher's exact tests for binary variables, Mann-Whitney U test for continuous variables, and Kruskal-Wallis test for multicategorical data.

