## 10.6 General Principles for Safety Analysis

Safety analysis includes:

- Analysis of patient discontinuation, dose reduction, or suspension due to adverse events;
- Incidence and severity of adverse events;
- Analysis of the relationship between adverse events and the drug;
- Analysis of the outcomes of adverse events;
- Analysis of serious adverse events;
- Descriptive statistical summary of laboratory, vital signs, and electrocardiogram data;
- Incidence of abnormal laboratory indicators;
- Analysis of positive abnormal changes in laboratory indicators, vital signs, and other data compared to baseline.

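### Glucose is defined only as above or not above normal, and the protocol does not say whether measured glucose, adjusted for its D0 value, will be compared between arms

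*Protocol*

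**What the plan says.** The Synopsis, under Secondary Safety Endpoints, lists "Blood glucose tracking (hyperglycemia defined as fasting/postprandial glucose exceeding normal ranges) during the first treatment week". It gives no numeric limits and no rule for reducing a patient's week of values to one result. Section 2.2.3 of the body names only "Treatment related adverse events (evaluated using the National Cancer Institute Common Terminology Criteria for Adverse Events (NCI CTCAE) version 5.0" and does not repeat glucose.

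The Study Flowchart row "Blood Glucose" is marked at D0 (headed Baseline), D1, D3, D5 and D7: one baseline and four later values per patient.

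Section 10.6 has three items that can cover glucose: "Descriptive statistical summary of laboratory, vital signs, and electrocardiogram data", "Incidence of abnormal laboratory indicators" and "Analysis of positive abnormal changes in laboratory indicators, vital signs, and other data compared to baseline". None names a test, a model or an estimate of the difference between arms.

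Section 10.5, headed as principles for efficacy analysis, says "Group comparisons employed chi-square/Fisher's exact tests for binary variables" and, in the same sentence, "Mann-Whitney U test for continuous variables". The sentence itself is not limited to efficacy variables. Section 1.3.1 justifies going from 8 mg to 5 mg by the hope of fewer and milder adverse reactions, and accepts that emesis control may be worse.

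**The concern.** An above/not-above outcome treats a value just over the limit and a very high value alike, and it counts a rise that stays within the range as nothing. It can show how often glucose is abnormal but not by how much, whereas intensity is part of the stated reason for the lower dose. Glucose is also the only metabolic measure among the named endpoints, and metabolic abnormality is one of the dexamethasone effects that Section 1.1 cites.

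The contrast is 3 mg in fewer than 100 patients per arm. If the cut were the basis of the comparison, a finding of similar hyperglycaemia rates would say little about whether the glucose effect had fallen. The values for a more informative comparison are already scheduled, but the text leaves open whether they will be used for one.

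**Working it through.** **The plan's own figure.** The protocol states no effect size, SD, prevalence or power for glucose. Its only sample-size figure is for complete response (Section 10.1: 80% in both arms, margin 15 points, one-sided 0.05, power 80%):

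n per arm = 2 × 0.80 × 0.20 × (1.645 + 0.842)² / 0.15² = 87.9, so 88 per arm and 176 in total; 176 / 0.95 = 185.3, so 186, or 93 per arm. This reproduces the protocol and supplies the 93 used below.

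**Assumed inputs, not in the protocol.** Glucose (or its logarithm) is normal with equal SD in both arms; the 5 mg arm lies d SD below the 8 mg arm; 20, 30 or 50% of the 8 mg arm exceeds the limit. The two-sided 0.05 level is the protocol's.

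**Binary comparison.** With p1 the proportion above the limit at 8 mg and z1 its normal cut point, p2 = 1 − Φ(z1 + d). Power = Φ[(p1 − p2 − 1.96·SE0) / SE1], where SE0 is the pooled and SE1 the unpooled standard error.

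Example with d = 0.4 and p1 = 0.30: z1 = 0.524 and p2 = 1 − Φ(0.924) = 0.178. SE0 = 0.0625 and SE1 = 0.0619. Power = Φ[(0.1224 − 0.1225) / 0.0619] = 49.9%.

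**One measured value by Mann-Whitney.** Power = Φ[d·√(93 × 0.955 / 2) − 1.96], where 0.955 is the asymptotic relative efficiency under normality. For d = 0.4: 0.4 × 6.664 − 1.96 = 0.706, giving 76.0%.

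| Shift d | Binary, 20% above | Binary, 30% | Binary, 50% | Mann-Whitney | Loss (points) |
|---|---|---|---|---|---|
| 0.2 SD | 14.9% | 17.1% | 19.0% | 26.5% | 8 to 12 |
| 0.3 SD | 27.0% | 31.9% | 36.6% | 51.6% | 15 to 25 |
| 0.4 SD | 41.8% | 49.9% | 57.5% | 76.0% | 18 to 34 |
| 0.5 SD | 57.0% | 67.2% | 76.2% | 91.5% | 15 to 35 |

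**Baseline adjustment.** If D0 correlates 0.5 with the later value (also assumed), analysis of covariance replaces d by d / √(1 − 0.25). Power becomes 66%, 88% and 98% at 0.3, 0.4 and 0.5 SD.

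**Sensitivity.** If only 10% exceed the limit at 8 mg, the loss is 16 to 53 points over shifts of 0.2 to 0.6 SD, measured here against a comparison of means. Using 88 per arm moves the losses by no more than about 2 points.

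A simulation of four correlated values (within-patient correlation 0.5, shifts 0.3 to 0.5 SD) looked at the whole week:

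- With the effect on all four days, classing a patient by any value above the limit lost about 9 to 42 points against Mann-Whitney on the weekly peak.
- With the effect on D1 only, any-value-above-limit had 7 to 18% power and Mann-Whitney on the D1 value had 51 to 91%. Mann-Whitney on the weekly peak had only 10 to 27%, so most of that gap comes from choosing the right time point, not from the scale.

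**The case against.** The strongest reply is that the protocol does not confine glucose to a yes/no test. The Section 10.5 sentence that gives chi-square or Fisher for binary variables goes on to give Mann-Whitney for continuous ones. If it governs safety data, measured glucose is covered. If it does not, no test of hyperglycaemia is planned either, and there is no planned power to lose. This stands against a firm claim that a chi-square comparison is the plan. What remains is that the text does not settle which reading applies, and that neither reading includes adjustment for D0.

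Four stronger readings are tempting and are not supported:

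- That measured values receive a descriptive summary only. Section 10.6 also plans the incidence of abnormal values and an analysis of abnormal changes from baseline. Both are built on abnormality, but they are more than description.
- That the endpoint is one yes/no result per patient for the week. The Synopsis speaks of tracking and fixes no per-patient rule.
- That the safety comparison as a whole loses power. No safety comparison is powered, and the calculation concerns glucose alone.
- That glucose is the only quantitative measure of steroid effect. ECG monitoring is also a named safety endpoint, and weight and blood pressure are measured; Section 1.3.1 links weight gain and hypertension to steroids. Only metabolic endpoint is accurate.

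It is also fair that the model for a safety laboratory variable often belongs in an SAP, which is not at hand, and that incidence of out-of-range glucose is conventional and easy to read. The point is therefore limited to what the protocol itself fixes: the endpoint definition, and safety wording that leaves the use of the measured values unclear.

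**Conclusion.** The concern holds as a cheap improvement, not as an error that threatens the trial. The protocol's only defined glucose outcome is above normal or not, and its text leaves open whether measured glucose is compared between arms and says nothing of adjusting for D0.

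If the cut is relied on, the loss for glucose is about 15 to 35 points of power at shifts of 0.3 to 0.5 SD and about 8 to 12 points at 0.2 SD. This rests wholly on the assumed shifts, prevalences and normal shape, and on one measured value as comparator. The direction was the same in every scenario computed.

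A reader might infer that the trial will report no difference in hyperglycaemia for want of power and would avoid this with measured values. That goes too far: at 0.2 SD Mann-Whitney itself has only about 27% power, and the documents give no basis for choosing among the shifts.

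**What to change.** State in the Synopsis endpoint and Section 10.6, and carry into Section 2.2.3 if glucose is to remain an endpoint, that the between-arm comparison uses measured post-dose glucose adjusted for D0. Either log glucose at D1, or a repeated-measures model of log glucose over D1 to D7 with arm, visit and D0 value, would serve. Analyse fasting and postprandial values separately and report the arm difference with its 95% CI. If an early, short-lived effect is expected, make D1 the main time point and not the weekly peak. Keep the incidence of hyperglycaemia alongside as a descriptive figure.

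The cost is a few sentences and no extra samples or visits. Two things must be in place: fasting or postprandial status recorded with every value, which the flowchart does not show, and confirmation that the D0 sample precedes dosing, since drug dispensation is marked at both D0 and D1. The downside is that a mean difference is less directly clinical than an incidence, which is why the incidence stays.
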